**Sample Size and Justification**

*Sample frame*

This study will take place in the Southern Province of Zambia in health facilities supported by ZCAHRD that are providing PMTCT and EID services at facility level. The sample frame comprises of 77 health facilities in Choma, Livingstone, and Monze districts. These districts were selected out the 10 districts in Southern Province based on leadership, geographic dispersion, urban / rural characteristics, current HIV prevalence rates, and absence of conflicting research projects. Hospitals and facilities without adequate skilled staff were excluded from the sample frame. The selection of Southern Province was made in conjunction with MoH officials who communicated that lessons learned from an evaluation in Southern Province could be generalized to other provinces in Zambia for purposes of scale up.

*Sample:* We will enroll a total of 11,910 participants into the study.

*Justification*

It has been determined that a sample of 60 facilities (20 facilities for each evaluation group) – selected out of the sample frame of 77 facilities – is required for the study.  The sample will be stratified by an urban/rural divide and district, with a third of the sites randomly chosen as comparison facilities, a third randomly chosen as Simple Intervention facilities, and the final third randomly chosen as Comprehensive Intervention facilities. Thus, the unit of randomization will be the health facility and all infants attending the given health facility for immunizations during the period of the evaluation will be the cluster.  Random assignment and post randomization checks will ensure that on average, observable and unobservable characteristics of the program and comparison groups are statistically similar. Observable characteristics that will be checked for balance across evaluation arms include baseline HIV testing rates, baseline immunization rates, number of ART sites, and catchment population sizes. In doing so, any difference in outcomes between program and comparison group can be causally attributed to the intervention. In total, we will have 60 clinics in the study, each of which see on average around 260 infants for their first immunization each year. To calculate the number of infants we expect to see, in our study, we divide 260 in half (we will only collect data for 6 months) and then we will take 75% of this remaining number (to account for around 25% of immunizations which will be done on outreach). This yields around 98 babies per facility multiplied by 60 facilities for a total of 5,880 infants. If we count mothers and infants as separate entities, we get a total of 11,760 participants. Up to 5% of the mothers/care givers in the study sample will be selected for data verification and a separate 5% of mothers will be selected for exit interviews, which is 294 mothers for each group. Additionally, up to 30 focus groups will be held, 15 for recent mothers and 15 with facility staff, with each focus group including no more than 10 individuals. The 150 mothers participating in the focus group are already included in the 11,760 participants. The 150 health facility staff participating in the focus groups are all new participants and must be added to the 11,760 participant number for a total of 11,910.

This study is designed to measure the impact of the Simple Intervention and Comprehensive Intervention on the number of women and infants tested and identified as HIV-positive as well as the percentage uptake of certain immunizations. Statistical power calculations are based on the immunization uptake outcome variable, as this is the indicator with the smallest effect size required to be policy-relevant. The study will test the following null hypotheses:

- - 1. Infants are not less likely to attend immunization clinics for DPT1, OPV1, DPT2 and OPV2 immunizations in Comprehensive Intervention health facilities versus the combination of the Simple Intervention and Comparison health facilities
    2. Rapid HIV antibody tests are not more likely to be administered in:
       1. Simple Intervention facilities versus Comparison facilities
       2. Comprehensive Intervention facilities versus Simple Intervention facilities
    3. DNA PCR tests are not more likely to be administered in:
       1. Simple Intervention facilities versus Comparison facilities
       2. Comprehensive Intervention facilities versus Simple Intervention facilities
    4. Mothers are not more likely to be identified as HIV-positive in:
       1. Simple Intervention facilities versus Comparison facilities
       2. Comprehensive Intervention facilities versus Simple Intervention facilities

Below are the power calculation for each of the outcomes we intend to measure:

*Effect of Comprehensive Intervention on immunization rates*

- **Level of outcome:** DPT 1 immunization
- **Sample:**
  - 20 Comprehensive Intervention facilities compared to 40 Simple Intervention and Comparison facilities
  - 98 new infants per facility
- **Detectable percentage point decrease in immunization uptake:** 10%
- **95% plausibility interval:** Expected probability that an infant receives DPT1 immunization is 87% with bounds around this estimate from 55 – 95%
- **Significance level:** 5%
- **Power:** 86%^[[29]](#footnote-7)^

*Effect of Simple Intervention on rapid HIV antibody testing rates (Simple versus Comparison facilities)*

- **Level of outcome:** Rapid HIV antibody tests administered
- **Sample:**
  - 20 Simple Intervention facilities compared to 20 Comparison facilities
  - 98 new infants per facility
- **Detectable percentage point increase in antibody tests:** 5%
- **95% plausibility interval:** Expected probability that a mother/infant pair receives a rapid HIV antibody test is 5% with bounds around this estimate from 1 - 10%
- **Significance level:** 5%
- **Power:** 87%

*Effect of Comprehensive Intervention on rapid HIV antibody testing rates (Comprehensive versus Simple facilities)*

- **Level of outcome:** Rapid HIV antibody tests administered
- **Sample:**
  - 20 Comprehensive Intervention facilities compared to 20 Simple Intervention facilities.
  - 98 new infants per facility
- **Detectable percentage point increase in antibody tests:** 20%
- **95% plausibility interval:** Expected probability that a mother/infant pair receives a rapid HIV antibody test is 15% with bounds around this estimate from 1 - 30%^[[30]](#footnote-8)^
- **Significance level:** 5%
- **Power:** 93%

*Effect of Simple Intervention on DBS PCR testing rates (Simple versus Comparison facilities)*

- **Level of outcome:** DBS PCR tests administered
- **Sample:**
  - 20 Simple Intervention facilities compared to 20 Comparison facilities
  - 98 new infants per facility
- **Detectable percentage point increase in DBS PCR tests:** 4%
- **95% plausibility interval:** Expected probability that an infant pair receives a DBS PCR test is 5%^[[31]](#footnote-9)^ with bounds around this estimate from 1 - 10%
- **Significance level:** 5%
- **Power:** 75%^[[32]](#footnote-10)^

*Effect of Comprehensive Intervention on DBS PCR test rates (Comprehensive versus Simple facilities)*

- **Level of outcome:** DBS PCR tests administered
- **Sample:**
  - 20 Comprehensive Intervention facilities compared to 20 Simple Intervention facilities
  - 98 new infants per facility
- **Detectable percentage point increase in DBS PCR tests:** 4%
- **95% plausibility interval:** Expected probability that a mother/infant pair receives a DBS PCR test is 9% with bounds around this estimate from 5 - 14%^[[33]](#footnote-11)^
- **Significance level:** 5%
- **Power:** 82%

*Effect of Simple Intervention on percentage of new mothers identified as HIV-positive (Simple versus Comparison facilities)*

- **Level of outcome:** HIV-positive mothers identified
- **Sample:**
  - 20 Simple Intervention facilities compared to 20 Comparison facilities.
  - 98 mother / infants pairs per facility
- **Detectable percentage point increase in HIV-positive mothers identified:** 0.8%
- **95% plausibility interval:** Expected probability that a mother is identified as HIV-positive is 0.2% with bounds around this estimate from 0.1 – 1.0%
- **Significance level:** 5%
- **Power:** 76%

*Effect of Comprehensive Intervention on percentage of new mothers identified as HIV-positive (Comprehensive versus Simple facilities)*

- **Level of outcome:** HIV-positive mothers identified
- **Sample:**
  - 20 Comprehensive Intervention facilities compared to 20 Simple Intervention facilities
  - 98 mother/infant pairs per facility
- **Detectable percentage point increase in HIV-positive mothers identified:** 1.5%
- **95% plausibility interval:** Expected probability that a mother is identified as HIV-positive is 1.0% with bounds around this estimate from 0.5% – 2.0%
- **Significance level:** 5%
- **Power:** 87%

These power calculations represent lower bounds, as covariate analysis will further increase the actual power of the evaluation. We can assume that because all research questions are sufficiently powered to detect effects between either the comprehensive and simple facilities or the simple facilities and the comparison facilities, all research questions are sufficiently powered to evaluate effects between the comprehensive and comparison clinics in the case where the simple clinics show no effect.

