- Operational integration of Early Infant Diagnosis (EID) and Expanded Program of Immunization (EPI)
- Training and orientation of health facility staff to deliver intervention messages to mothers of children under five years

1. Control: Usual standard of care.

We will then evaluate the two interventions in comparison to the control group, as well compare the two intervention groups to each other, in terms of specific outcomes (See the power calculations section for specific outcome variables) by a review of clinic records collected over the period of the study.

We will supplement and triangulate the data obtained from the clinic records through four primary data collection tools:

- Focus Group #1: Mothers who have recently attended Under-5 clinics
- Focus Group #2: Health facility workers in sampled health facilities Interview guide for exit interviews for mothers done at health facilities
- Interview guide for data verification for mothers done in local communities

Random sampling will be done at the health facility level to separate health facilities in the sample frame into 4 groups – 1) Comparison 2) Simple Intervention 3) Comprehensive Intervention and 4) Not in the study sample. Sampling will be conducted using STATA IC Version 12 with a pre-set seeds to allow for post-randomization verification of selection methods. There are 77 clinics in the sample frame spread across three districts in Southern Province in Zambia. The sample will be stratified by urban/rural divide and by district. Please see the table below for information on the stratification within the sample frame and sample respectively.

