**Table 1: Sample Stratification**

|  | Total Facilities | Total Urban | Total Rural | Sample Total | Sample Urban | Sample Rural |
| --- | --- | --- | --- | --- | --- | --- |
| Choma | 37 | 6 | 31 | 30 | 6 | 24 |
| Livingstone | 15 | 11 | 4 | 9 | 9 | 0 |
| Monze | 25 | 3 | 22 | 21 | 3 | 18 |
| Total | 77 | 20 | 57 | 60 | 18 | 42 |

Sampling of clinics will not be weighted by population; therefore, individuals who live in facilities with smaller catchment areas have slightly higher probability of being included in the study than those that live in the catchment area of larger facilities. Within each strata, each facility has an equal chance of being allocated into each of the three evaluation arms. Randomization will not occur on site but will be conducted before the interventions begin. Please note, at the time of submission to IRB, the final sample has not been run in STATA.

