28. First immunizations refer to the 6-week visit for under-five health facility where children receive the following vaccinations: OPV1 and DPT1-HepB-HiB. The Second immunization refers to the 10-week visit to under-five health facility for OPV2 and DPT2 vaccines. [↑](#footnote-ref-6)
29. Analysis will include the use of historical immunization data as covariates which will increase power to a level greater than 80%. For the sample frame, at least 60 to 70% of the variation in immunization rates on a month to month basis can be explained by the previous year of data. [↑](#footnote-ref-7)
30. This assumes that the simple intervention will have the effect assumed in the previous power calculation because this calculation compares comprehensive clinics to simple clinics. [↑](#footnote-ref-8)
31. This assumes that of the approximately 45,000 babies tested currently for a DNA PCR, around two-thirds are first test PCR (done at around the 6-week time frame) and the remaining 1/3 are retests. This means that 30,000 out 600,000 babies born each year receive a PCR test at 6 weeks - around 5%. [↑](#footnote-ref-9)
32. As in the case of the immunization data, covariates will be used to increase power for this outcome [↑](#footnote-ref-10)
33. This assumes that the simple intervention will have the effect assumed in the previous power calculation because this calculation compares comprehensive clinics to simple clinics. [↑](#footnote-ref-11)
34. A linear regression measuring the effect of the Comprehensive Intervention on immunization uptake will be used to assess any decrease in immunizations. “Confirmed” indicates a drop of 20 percentage points is observed at a 95% confidence level. [↑](#footnote-ref-12)
35. National Protocol Guidelines, Integrated Prevention of Mother-to-Child Transmission of HIV/AID in Zambia, 2008 Page 8. [↑](#endnote-ref-23)

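### Constraining the not-yet-run draw on the baseline variables that are now only checked afterwards is a cheap precision gain, worth about 2 to 4 points of power on the PCR and HIV-positive contrasts

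*Protocol*

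**What the plan says.** Under Sample Size and Justification, the Protocol takes 60 facilities, 20 per arm, and states: "Random assignment and post randomization checks will ensure that on average, observable and unobservable characteristics of the program and comparison groups are statistically similar". It goes on: "Observable characteristics that will be checked for balance across evaluation arms include baseline HIV testing rates, baseline immunization rates". The list also covers ART sites and catchment size. No test, threshold or consequence is given for the check.

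On what is built into the draw, Study Design and Procedures says: "The sample will be stratified by urban/rural divide and by district". Table 1 gives five non-empty strata: Choma urban 6 and rural 24, Livingstone urban 9, Monze urban 3 and rural 18. Each divides by three.

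On timing, the text after Table 1 says "Randomization will not occur on site but will be conducted before the interventions begin" and that "at the time of submission to IRB, the final sample has not been run in STATA".

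Data Analysis makes a logit regression primary and lists as covariates historical EID and EPI rates, district, catchment population, facility staff, geography and patient characteristics. Number of ART sites is not named. Separately, note 34, on the discontinuation rule for the Comprehensive Intervention, says "A linear regression measuring the effect of the Comprehensive Intervention on immunization uptake will be used to assess any decrease in immunizations" and names no covariates.

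**The concern.** Four facility-level variables that may predict the outcomes are left to chance in the draw, and a later check is then credited with making the arms similar. A check can only report what the draw produced. With 20 facilities per arm, some imbalance on at least one of four variables is likely. In an adjusted model the arm indicator is then partly collinear with the covariates, and the standard error of the arm effect rises.

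What is at stake is precision. Two contrasts start at a stated 75% (PCR, Simple v Comparison) and 76% (HIV-positive mothers, Simple v Comparison). A few points matter there, and they can be recovered only before the allocation is drawn.

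**Working it through.** **1. Reproduce the stated power.** PCR, Simple v Comparison: 20 v 20 facilities, 98 infants each, 5% to 9%, bounds 1 to 10%, alpha 5% (taken as two-sided).

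- Between-facility variance on the logit scale: τ² = [(logit 0.10 − logit 0.01)/3.92]² = (2.398/3.92)² = 0.374.
- Variance of the contrast: [0.374 + 1/(98 × 0.05 × 0.95) + 0.374 + 1/(98 × 0.09 × 0.91)]/20 = (0.374 + 0.215 + 0.374 + 0.125)/20 = 0.0544, so SE = 0.233.
- Effect: logit 0.09 − logit 0.05 = 0.631. Ratio to SE = 2.705.
- Noncentral F with 1 and 38 df: power 75.0%. Stated: 75%.

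The same method gives 76.9% (stated 76), 83.0% (82) and 87.5% (87) for the other PCR and HIV-positive contrasts, and 88.1% (87) and 93.6% (93) for rapid testing. Immunization gives 91.4% against a stated 86%. That mismatch is a separate matter, and the immunization row below uses the recomputed base.

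**2. Variance inflation from imbalance.** For a 20 v 20 contrast the factor is 10/RSS, where RSS is the residual sum of squares of the arm indicator regressed on the covariates, and 10 = 40 × 0.5 × 0.5 is its total sum of squares.

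- Planned draw, simulated in the Table 1 strata with four independent normal covariates: mean factor 1.122. As a check, plain random allocation has expectation (N − 3)/(N − 3 − k) = 37/33 = 1.121 for N = 40 and k = 4. With district and urban/rural also in the model the factor is 1.13 to 1.14.
- Best-balanced 10% of draws: 1.039.
- 20 v 40 (immunization): 1.077 falling to 1.025.

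In the same simulation, the chance that at least one of the four variables differs by more than 0.5 SD between some pair of arms falls from 71% to 1.6%. Strata that explain part of these variables would lower the first figure.

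**3. Power, planned draw to constrained draw.** Replace τ² by τ²(1 − R²), multiply the variance by the factor from step 2, and use 34 df (54 for immunization). R² is the share of between-facility variance explained by the covariates. The range 0 to 0.65 is an assumption. Note 29 supports a high value for immunization only, and there it describes month-to-month variation.

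| Contrast | R² = 0 | R² = 0.3 | R² = 0.65 |
|---|---|---|---|
| PCR, Simple v Comparison | 69.9 to 73.2% | 79.5 to 82.5% | 91.6 to 93.4% |
| HIV-positive, Simple v Comparison | 71.8 to 75.1% | 73.1 to 76.3% | 74.7 to 77.9% |
| PCR, Comprehensive v Simple | 78.3 to 81.3% | 83.7 to 86.4% | 90.0 to 92.0% |
| HIV-positive, Comprehensive v Simple | 83.3 to 86.0% | 85.0 to 87.5% | 86.9 to 89.3% |
| Immunization, 20 v 40 | 89.3 to 90.7% | 96.2 to 96.9% | 99.8 to 99.9% |

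The gain is about 2 to 3 points on the first four rows. With stratum terms in the model it reaches 3.7 points for PCR, Simple v Comparison, and 1.5 points for immunization. For the rapid-test contrasts the simulated gain is 0.1 to 3.0 points.

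**4. Is enough randomness left?** The number of stratified allocations is the product over strata of m!/[(m/3)!]³ for m = 6, 24, 9, 3, 18, about 1.5 × 10²³. Ten per cent of that is still about 1.5 × 10²².

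**The case against.** The strongest reply is that nothing here is broken, and most of that reply stands. The strata are balanced by design. The phrase on average is correct for random assignment; only the credit given to the checks is wrong. Data Analysis already adjusts for historical testing and immunization rates and for catchment size.

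Several stronger readings are tempting, and the document does not support them:

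- *The arms may be biased.* Chance imbalance under a random draw does not bias the effect estimate, and the planned adjustment deals with most of what occurs.
- *True power is about 70% for the weakest contrast.* That holds only if the covariates explain nothing. The Protocol calls its stated powers lower bounds because of covariate analysis, and note 32 relies on covariates for this contrast. At R² = 0.3 the planned draw already gives 79.5%.
- *The balance check will often fail and force an informal redraw.* No test or threshold is named, so a failure rate cannot be computed. Adjustment is the planned response, and the pre-set seed allows the selection to be verified.
- *Baseline immunization imbalance adds to the error already planned for.* This chance spread is part of the between-facility variance in the power calculation and should not be counted twice.
- *The note 34 regression is unadjusted.* It is silent on covariates, and silence does not settle the point.

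It is also fair to say that the data may not all be ready. Note 29 implies prior-year immunization data for the frame, but nothing says that DBS and antibody baselines will be compiled before the draw.

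What does not stand is that this is only a matter of taste. The gain is present in every adjusted PCR and HIV-positive contrast examined, and it is lost once the draw is run.

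**Conclusion.** The point holds as a cheap improvement together with a wording correction. Under the planned draw, imbalance on four baseline covariates inflates the variance of adjusted 20 v 20 contrasts by about 12 to 14%, against about 4% after constraint. That is worth about 2 to 4 points of power on the PCR and HIV-positive contrasts and at most about 1.5 points on adjusted immunization. A reader should not carry the upper end over to all outcomes, because the gain shrinks where covariates are strong or power is already high.

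The figures assume four independent, normally distributed facility covariates, R² between 0 and 0.65, retention of the best 10% of draws, and an analysis that includes the constraining covariates.

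**What to change.** Before the Stata draw is run:

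1. Generate many allocations within the existing district by urban/rural strata. Score each on the standardised differences across the three arms in baseline immunization, baseline DBS testing, baseline antibody testing, catchment size and number of ART sites, as far as these are available for the frame. Keep the best-balanced fraction, for example 10%, and select one with the pre-set seed.
2. Keep those variables in the primary model, adding number of ART sites, and name them in the note 34 regression.
3. Draw any permutation test from the retained set only.
4. Replace the statement that post-randomization checks ensure similarity with a commitment to a descriptive baseline table by arm.

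The cost is a few lines of code and a short protocol edit. There are two real conditions: baseline register data must be compiled before the draw, and the analysis must keep the constraining covariates, most of which are already planned.

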Zambia’s MoH and international partners have invested in improving the infrastructure and systems necessary to increase EID testing services in recent years. EID is now available in over 800 health facilities in all 10 provinces. There are currently two DNA PCR labs in Lusaka, one in Ndola, and additional labs scheduled to open in Chipata and Livingstone. The Zambia Centre for Applied Health Research and Development (ZCAHRD), the implementing partner for this evaluation, is also scaling up an SMS-based test results reporting platform that halves the time required to return EID test results to health facilities. Once operational, these additional DNA PCR labs and SMS services will reduce the transport burden for time-sensitive lab results and increase the nation’s overall HIV testing capacity. Given Zambia’s increasing HIV laboratory infrastructure, it is an appropriate moment to explore opportunities to increase the nation’s overall EID testing rates.

Study Objectives and Context

The primary objectives of the study are to assess the impact of:

1. Study interventions on EID testing rates of HIV-exposed infants
2. Study interventions on the number of women identified to be HIV-positive
3. The Comprehensive Intervention on infant immunization uptake

Secondary objective include:

1. Estimating the incidence of HIV among women who previously tested negative for HIV during pregnancy
2. Evaluating the cost-effectiveness of the Simple Intervention versus the Comprehensive Intervention.

The primary goal of this study is to evaluate different measures that might improve EID testing rates and identification of HIV-positive mothers and babies without negatively affecting uptake of immunization services. Identifying such measures has recently become highly relevant due to the Zambian government’s recent announcement to support a strategy of universal HIV testing and implementation of Option B+ nationwide as a strategy to eliminate mother-to-child transmission of HIV.^[[13]](#footnote-1)^ ^[[14]](#endnote-13)^ Critical to the success of Option B+ is the need to make sure that a high percentage of women are tested for HIV and placed on treatment if discovered to be HIV-positive. For this reason, the study intervention is also designed to increase the number of new mothers that are tested for HIV.

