A study of infected and uninfected infants born to HIV-positive mothers found that babies that were identified early and introduced to treatment had significantly better mortality outcomes than those who did not immediately go on treatment. At 1 year of age, 35.2% of infected infants died without treatment and 52.5% had died by 2 years of age without treatment.^[[23]](#endnote-22)^

*Contribution of Evaluation to Literature*

This proposed study will contribute to the literature in several important ways. First, it will assess the extent to which integration of universal HIV testing with routine under-five immunizations, similar to current practice with ANC, can boost HIV testing rates without negatively impacting uptake of immunization. Secondly, it would inform Zambia and other high HIV prevalence countries whether either intervention could be a cost effective approach to identifying new HIV positive infants and mothers. Finally, this study will provide insight into the feasibility of integrating HIV into other public health services.

Study Significance
This evaluation will be the second evaluation launched under the Demand Driven Evaluations for Decisions (3DE) initiative, a three-year partnership between the Clinton Health Access Initiative (CHAI), IDinsight, Zambia’s MoH, and Zambia’s MoCDMCH. By using rigorous impact evaluations in a demand-driven and efficient manner, 3DE seeks to generate reliable impact evidence to catalyze at-scale implementation of cost-effective policies.

The evaluation will help Zambia’s MoH and MoCDMCH determine if the Simple Intervention or Comprehensive Intervention can cost-effectively improve HIV testing rates and the identification of HIV-positive and HIV-exposed mothers and babies without harming under-five immunization uptake. Furthermore, the evaluation will illuminate the operational requirements of these activities, including requirements for funding, staff, training, communication, equipment and logistics. The results of this evaluation will inform the potential scale up of either intervention as well as broad policy decisions on the possibility of integrating HIV services more closely with other existing patient touch points.

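### The immunization hypothesis can show a fall in uptake but gives no rule for concluding that a relevant fall has been excluded, which is what the primary goal asks

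*Protocol*

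**What the plan says.** Protocol, Study Objectives and Context, sets the primary goal as better infant testing and identification "without negatively affecting uptake of immunization services". Study Significance says the results will help the ministries judge whether either intervention can do this "without harming under-five immunization uptake".

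Sample Size and Justification lists the null hypotheses. The first is: "Infants are not less likely to attend immunization clinics for DPT1, OPV1, DPT2 and OPV2 immunizations in Comprehensive Intervention health facilities", with the Simple and Comparison facilities combined as comparator. Power is based on immunization uptake because "this is the indicator with the smallest effect size required to be policy-relevant". The inputs for this outcome are:

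- "20 Comprehensive Intervention facilities compared to 40 Simple Intervention and Comparison facilities"
- "98 new infants per facility"
- "Detectable percentage point decrease in immunization uptake: 10" (percent)
- "Expected probability that an infant receives DPT1 immunization is 87% with bounds around this estimate from 55 – 95" (percent)
- significance level 5%, with sidedness not stated
- power 86%

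Data Analysis adds a multilevel logit regression with covariates, including historical immunization rates. The only other numerical threshold for immunization is the 20-point discontinuation rule under Ethical Issues, which acts only on a drop confirmed at 95% confidence. The protocol gives no margin and no confidence-limit rule for concluding that uptake was not harmed.

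**The concern.** Hypotheses 2 to 4, on HIV testing and identification, are framed in the usual way: rejecting the null supports the intervention. Hypothesis 1 uses the same template, but its favourable answer is the null itself. A significance test can reject that null; it cannot establish it. Failing to reject is also easier when the data are noisier, for example with fewer facilities or poorer registers.

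A scale-up recommendation needs a statement that immunization has not suffered to a degree that matters. The protocol fixes the hypothesis and its direction but gives no criterion for making that statement. One of the three primary objectives therefore has a rule for the unfavourable conclusion and none for the favourable one.

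**Working it through.** **Inputs** (Sample Size and Justification): comparator uptake 87%; bounds 55–95%, read as a 95% range across facilities; 98 infants per facility; 20 versus 40 facilities; 5% significance. The covariate figure of 60–70% comes from the power footnote, where it describes month-to-month variation. Applying it to between-facility variance is my assumption.

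**Model.** Log-odds scale, noncentral t with 20 + 40 − 2 = 58 df.

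- Between-facility variance: τ = ((logit 0.95 − logit 0.55)/3.92)² = ((2.944 − 0.201)/3.92)² = 0.490
- SE = √[(τ + s²/98)(1/20 + 1/40)], where s² is the average of 1/(p(1−p)) over the two rates

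**Plan's own figure (10-point fall, 87% to 77%).**

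- s² = (8.842 + 5.647)/2 = 7.244
- SE = √[(0.490 + 0.074) × 0.075] = 0.206
- Effect = 1.901 − 1.208 = 0.693; ratio 3.37
- Power 91% two-sided or 95% one-sided, against 86% stated

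The same two-sided formula gives 88, 94, 75, 83, 77 and 88% for the other six comparisons, against 87, 93, 75, 82, 76 and 87% stated. The method therefore fits, and only the immunization figure differs. That mismatch is a separate matter, so results are also given from the stated 86%.

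**Chance that the stated test is non-significant.** For a true 5-point fall (87% to 82%), the effect is 1.901 − 1.516 = 0.385. Without covariates SE = 0.207 and the ratio is 1.86. With 60% or 70% of τ removed, SE = 0.144 or 0.130 and the ratio is 2.67 or 2.95.

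| True fall | Two-sided, no covariates | One-sided, no covariates | Two-sided, 60–70% of τ removed |
|---|---|---|---|
| 5 points | 55% | 42% | 17–25% |
| 10 points | 9% | 5% | under 1% |

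From the stated 86% power, the implied SE is 10/(1.960 + 1.080) = 3.29 points if the test is two-sided, or 10/(1.645 + 1.080) = 3.67 points if one-sided. The chance of non-significance is then 67% or 61% at a 5-point fall and 14% at 10 points.

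**Power of a non-inferiority criterion when there is no true fall** (one-sided 2.5%, the lower limit of a two-sided 95% interval). With both rates at 87%, SE = √[(0.490 + 8.842/98) × 0.075] = 0.209.

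| Margin | No covariates | 60–70% of τ removed | From stated 86% power |
|---|---|---|---|
| 10 points | 0.693/0.209 = 3.32, so 90% | over 99% | 78–86% |
| 5 points | 0.385/0.209 = 1.84, so 44% | 73–81% | 28–33% |

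**Would a 10-point margin alone protect better than the present test?** For a true 5-point fall, the distance to the margin is logit 0.82 − logit 0.77 = 1.516 − 1.208 = 0.308. Divided by SE 0.207 this is 1.49, and the criterion is met in 31% of trials. With the assumed covariate gain the ratios are 2.14 and 2.36, and it is met in about 56–64%. The present test misses such a fall in only 17–25% under the same assumption. A 10-point criterion used in place of the test could therefore be the more permissive rule.

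**The case against.** A reader might infer that the protocol plans to read a non-significant result as proof of safety. It does not say so. Study Aims and Data Analysis speak of estimating impacts and comparing percentages, and an estimate with its interval could be interpreted properly. What stands is narrower: no rule is stated for reaching the favourable conclusion.

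A reader might also infer that the risk of missing a fall is uncontrolled. That is too strong. The trial is sized on this outcome, and at the stated power a 10-point fall would be missed 14% of the time. The protocol calls its power figures lower bounds because covariates will be used, and the null is directional, so a one-sided test is possible. The 55% is thus the least favourable reading of the plan's inputs and is shown with its alternatives.

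The design also leans towards finding harm, because patients who transfer away count as lost uptake, and the discontinuation rule gives some monitoring. Neither supplies a criterion for excluding a relevant fall.

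It is tempting to treat 10 points as the policy threshold, since power is based on immunization as "this is the indicator with the smallest effect size required to be policy-relevant". But the protocol labels 10 points a detectable decrease and nowhere defends it as a tolerable loss. Other outcomes in the same section have smaller detectable differences, down to 0.8 points.

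Finally, interval reporting often belongs in a statistical analysis plan, which was not available. The hypothesis and its direction, however, are fixed in the protocol itself.

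**Conclusion.** The point holds in this form. The goal requires evidence that immunization was not harmed; the stated hypothesis can only supply evidence that it was; and no margin or interval rule bridges the two.

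The practical gap lies at falls smaller than the design effect. A true 5-point fall goes undetected in 55% (two-sided) or 42% (one-sided) of trials without covariates, in about 17–25% (two-sided) with the assumed covariate gain, and in 61–67% on the standard error implied by the stated power. At 10 points the gap is small: 9% or less as recomputed, 14% as stated.

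These figures rest on reading the plausibility bounds as between-facility spread, on equal facility sizes of 98, and, for the covariate results, on carrying the 60–70% over to between-facility variance. The logical point depends on none of them.

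**What to change.** Keep the test for a decrease. Add to the hypotheses in Sample Size and Justification a non-inferiority criterion for DPT1 and DPT2:

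- Conclude no harm only if the two-sided 95% confidence interval for Comprehensive minus the combined Simple and Comparison facilities excludes a fall as large as a pre-specified margin.
- The sponsor and ministries fix and justify that margin before analysis. The 10-point detectable fall is an upper limit for it, not a justification.
- Report a significant decrease as a decrease even when the margin is met.
- Do not report a non-significant difference as no effect.

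State whether the 5% is one- or two-sided.

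The cost is protocol wording; no further facilities or data are needed for a 10-point margin. A tighter margin has lower power, and a 5-point margin would depend on a large covariate gain. An inconclusive interval could no longer support a statement of no harm.
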